## Abstract

**Introduction::**

Globally, colorectal cancer (CRC) is the third most commonly diagnosed cancer in males and the second in females. Rectal cancer (RC) accounts for about 28% of all newly diagnosed CRC cases. The treatment of choice for locally advanced RC is a combination of surgical resection and chemotherapy and/or radiotherapy. These patients can potentially be cured, but the clinical outcome depends on the tumor biology. Microsatellite instability (MSI) is an important biomarker in CRC, with crucial diagnostic, prognostic, and predictive implications. It is important to develop a noninvasive, repeatable, and reproducible method to reflect the microsatellite status. Magnetic resonance imaging (MRI) has been recommended as the preferred imaging examination for RC in clinical practice by both the National Comprehensive Cancer Network and the European Society for Medical Oncology guidelines. T2WI is the core sequence of MRI scanning protocol for RC. Radiomics, the high-throughput mining of quantitative image features from standard-of-care medical imaging that enables data to be extracted and applied within clinical-decision support systems to improve diagnostic, prognostic, and predictive accuracy, is gaining importance in cancer research.

We proposed a hypothesis: A simple radiomics model based on only T2WI images can accurately evaluate the MSI status of RC preoperatively.

**Objective::**

To develop a radiomics model based on T2WI images for accurate preoperative diagnosis the MSI status of RC.

**Method::**

All patients with RC were retrospectively enrolled. The dataset was randomly split into training cohort (70% of all patients) and testing cohort (30% of all patients). The radiomics features will be extracted from T2WI–MR images of the entire primary tumor region. Least absolute shrinkage and selection operator was used to select the most predictive radiomics features. Logistic regression models were constructed in the training/validation cohort to discriminate the MSI status using clinical factors, radiomics features, or their integration. The diagnostic performance of these 3 models was evaluated in the testing cohort based on their area under the curve, sensitivity, specificity, and accuracy.

**Discussion::**

This study will help us know whether radiomics model based on T2WI images to preoperative identify MSI status of RC.

## Introduction

1

Globally, colorectal cancer (CRC) is the third most commonly diagnosed cancer in males and the second in females, with 1.8 million new cases and almost 861,000 deaths in 2018.^[1]^ Rectal cancer (RC) accounts for about 28% of all newly diagnosed CRC cases.^[2]^ The treatment of choice for locally advanced RC is a combination of surgical resection and chemotherapy and/or radiotherapy. These patients can potentially be cured, but the clinical outcome depends on the tumor biology.^[3]^

Microsatellite instability (MSI) is an important biomarker in CRC, with crucial diagnostic, prognostic, and predictive implications. MSI-high (MSI-H) status is associated with a better prognosis in early-stage CRC and a lack of benefit from adjuvant treatment with 5-fluorouracil in stage II disease, and these patients have shown a significantly better prognosis than those characterized by microsatellite stability (MSS).^[4]^ More recently, MSI has emerged as a predictor of sensitivity to immunotherapy-based treatments.^[4,5]^ Therefore, MSI testing is recommended by the National Comprehensive Cancer Network (NCCN) guidelines for all patients with stage II RC,^[6]^ and the European Society for Medical Oncology (ESMO) also recommended MSI testing for cancer immunotherapy in 2019.^[7]^ Preoperative evaluation of MSI status can be performed only by biopsy. However, first, tumors have spatial and temporal heterogeneities,^[8]^ the result of MSI testing may vary depend on where and when the specimen are obtained. Second, The risks of invasive sampling and potential complications. Therefore, it is important to develop a noninvasive, repeatable, and reproducible method to reflect the microsatellite status.

The conversion of digital medical images into mineable high-dimensional data, a process that is known as radiomics, is motivated by the concept that biomedical images contain information that reflects underlying pathophysiology and that these relationships can be revealed via quantitative image analyses.^[9]^ Recent studies of RC have showed encouraging evidence that radiomics can be applied to predict characteristics including therapeutic responses,^[10,11]^ lymph node metastasis,^[12,13]^ and Kirsten sarcoma viral oncogene homologue mutations.^[14,15]^ And, the radiomics based on computed tomography images can predict the MSI status of CRC was reported in 2 recent studies.^[16,17]^ Magnetic resonance imaging (MRI) has been recommended as the preferred imaging examination for RC in clinical practice by both NCCN^[18]^ and ESMO^[19]^ guidelines. T2WI is the core sequence of MRI scanning protocol for RC.^[20]^

We proposed a hypothesis: a simple radiomics model based on only T2WI images can accurately evaluate the MSI status of RC preoperatively.

## Participants and methods

2

### Study aims

2.1

The aim of this study is to develop a radiomics model based on T2WI images for accurate preoperative diagnosis the MSI status of RC.

### Study design/setting

2.2

This is a single-center, retrospective, cross-sectional clinical study. The T2WI data were anonymous.

### Study registration

2.3

This clinical trial has been registered on the Chinese Clinical Trial Registry (www.chictr.org.cn), and the registration number is ChiCTR2000029362.

### Eligibility criteria (Fig. 1)

2.4

The patients with RC underwent surgery at our hospital from January 2016 to May 2019 were retrospectively collected.

**Figure 1 F1:**
[figure not shown]
Flowchart of the patient selection and patient exclusion.

#### Inclusion criteria

2.4.1

(1)Pathologically confirmed as adenocarcinoma.(2)MRI within 2 weeks before surgery.

#### Exclusion criteria

2.4.2

(1)Without MSI evaluation.(2)Receiving chemoradiotherapy before MRI.(3)Small tumors (<5 mm) difficult to identify on images.(4)Insufficient T2WI quality to draw the region of interest (ROI) such as obvious motion artifact caused by respiration or intestinal peristalsis.(5)Mucinous adenocarcinoma.

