#### MRI image acquisition and segmentation

2.6.2

All patients underwent MRI scan following protocol for RC within 2 weeks before surgery or biopsy. By using the ITK-SNAP software (v3.6.0, http://www.itksnap.org), the tumor region was manually segmented volumetrically by a radiologist with more than 10 years of experience in abdominal imaging on all oblique axial (angulated perpendicular to the long axis of the rectal tumor) of T2WI slices. The necrosis area, intraluminal air regions, and uninvaded rectal wall were excluded from the ROIs with caution. In case that the boundary was uncertain, a final decision was made by another radiologist with 20 years of experience in abdominal diagnosis.

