### Sample size calculation

2.9

We calculated the number of patients needed considering the epidemiology of MSI in RC and previous report by Wu et al.^[21]^ Test for 1 receiver operating characteristic (ROC) curve analysis showed that a sample of 33 from the MSI group and 297 from the MSS group could achieve 95% power to detect a difference of the null hypothesis (area under the curve [AUC] = 0.70) and the alternative hypothesis (AUC = 0.85), which was calculated by PASS 2019 (NCSS Statistical Software).

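### The prior-treatment exclusion names only chemoradiotherapy, so as written it can admit tumours imaged after chemotherapy alone or radiotherapy alone

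*Protocol article*

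**What the plan says.** Exclusion criterion (2) of the Protocol article (section 2.4.2) reads "Receiving chemoradiotherapy before MRI". No other criterion in sections 2.4 to 2.4.2 mentions prior treatment, and none requires an untreated tumour.

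The source population is surgical: "The patients with RC underwent surgery at our hospital from January 2016 to May 2019 were retrospectively collected". The timing criterion in section 2.4.1 is "MRI within 2 weeks before surgery". The imaging section (2.6.2) gives a different window: "All patients underwent MRI scan following protocol for RC within 2 weeks before surgery or biopsy".

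The Introduction describes treatment in these terms: "The treatment of choice for locally advanced RC is a combination of surgical resection and chemotherapy and/or radiotherapy".

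The Abstract states that the dataset was split at random, 70% for training and 30% for testing. The stated aim (section 2.1) is to diagnose MSI status preoperatively from T2WI.

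**The concern.** The evident purpose of criterion (2) is to keep treatment change out of the T2WI features. That reason applies to chemotherapy alone and to radiotherapy alone as much as to the two together, yet only the combined form is named. The cohort is assembled retrospectively from records, so the wording of the criterion decides who is in it.

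If treated tumours enter, their shape, intensity and texture features partly describe response to treatment. Features that would separate MSI from MSS in untreated tumours may then do so less well, or differently. A random split within one centre gives training and testing cohorts the same expected mix of treated and untreated images. The testing AUC would describe that mix and could not reveal the problem.

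**Working it through.** **1. The criteria applied to a hypothetical patient.** Take a patient with adenocarcinoma who had chemotherapy alone (or radiotherapy alone), then MRI, then surgery within 2 weeks, with MSI evaluated.

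| Criterion | Result |
|---|---|
| Adenocarcinoma on pathology | met |
| MRI no more than 2 weeks before surgery | met |
| MSI evaluation missing | not excluded |
| Chemoradiotherapy before MRI | not excluded, on the literal wording |
| Tumour under 5 mm, poor T2WI quality, mucinous type | not excluded, unless separately present |

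The patient is eligible. The imaging section does not close the gap. A scan shortly before biopsy would normally precede treatment, but a scan shortly before surgery need not, and the article gives both windows.

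**2. The plan's own figure.** Section 2.9 states that "a sample of 33 from the MSI group and 297 from the MSS group could achieve 95% power" for AUC 0.70 against 0.85. The textual point does not depend on this figure, but it sets the scale. With the Hanley–McNeil variance,

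V(t) = [t(1−t) + (n1−1)(Q1−t²) + (n0−1)(Q2−t²)] / (n1·n0), where Q1 = t/(2−t), Q2 = 2t²/(1+t), n1 = 33 and n0 = 297,

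the standard errors are 0.0528 at AUC 0.70 and 0.0429 at AUC 0.85.

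- Variance under the alternative only, two-sided 5%: Φ(0.15/0.0429 − 1.96) = 93.8%, close to the stated 95%. Binormal and Obuchowski variances give 95.3% one-sided.
- Null variance for the critical value and alternative variance for power, two-sided: Φ((0.15 − 1.96×0.0528)/0.0429) = 86.1%.

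The stated power is thus reproduced under some variants of the test. The second variant is used below because it allows the AUC to change.

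**3. Size of dilution, by assumption.** The article gives no share of patients treated with one modality, so a range is shown. Assumptions: equal-variance binormal scores; AUC 0.85 in untreated tumours; a share f treated in both MSI and MSS; treated tumours carry no signal and score midway between the groups.

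- Separation: d′ = √2 × Φ⁻¹(0.85) = 1.466.
- AUC for a pair with one treated and one untreated tumour: Φ(d′/(2√2)) = 0.698.
- Overall: AUC(f) = (1−f)²×0.85 + 2f(1−f)×0.698 + f²×0.5.

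| f | AUC | Share of the 0.15 margin over 0.70 that is lost |
|---|---|---|
| 5% | 0.7671 + 0.0663 + 0.0013 = 0.835 | 10% |
| 10% | 0.6885 + 0.1256 + 0.0050 = 0.819 | 21% |
| 20% | 0.5440 + 0.2233 + 0.0200 = 0.787 | 42% |

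**4. Keeping or removing these patients, on the same assumptions.** Keeping all 330: power = Φ((AUC(f) − 0.70 − 1.96×0.0528)/SE), with SE = 0.0444, 0.0459 and 0.0484 at the three AUCs. Removing them without replacement: AUC 0.85, with the variances recomputed for the smaller groups.

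| f | Power, kept | Power, removed (MSI/MSS left) |
|---|---|---|
| 0% | 86% | 86% (33/297) |
| 5% | 76% | 84% (31/282) |
| 10% | 63% | 82% (30/267) |
| 20% | 37% | 76% (26/238) |

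If treated images really carry no signal, removal costs less power than retention at every share shown.

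**The case against.** Four objections deserve weight.

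**It may be shorthand.** In a condensed article, chemoradiotherapy can stand for chemotherapy and/or radiotherapy, and the selection flowchart (Figure 1) is not available here. This stands as a reason for caution: the investigators may already have excluded these patients. It does not remove the gap, because the criterion as printed is narrower than its purpose and the same article separates the modalities elsewhere.

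**The Introduction's sentence is general background.** It gives no timing, so it includes postoperative treatment, and it does not describe this centre's practice. That is correct. It shows that the article distinguishes the modalities, not that anyone received one of them before MRI.

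**The magnitudes are assumed.** Correct. At 5% the loss is small, and under these assumptions dilution is conservative because it lowers the AUC.

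**Treatment steered by MSI status.** A reader might go further and infer that treatment before MRI depended on MSI, so that treatment change would act as a proxy for the label and inflate the AUC. The Introduction does mention "a lack of benefit from adjuvant treatment with 5-fluorouracil in stage II disease", and immunotherapy sensitivity. But adjuvant treatment follows surgery and cannot alter a preoperative scan. Nothing shows that MSI was known early enough, or used, to choose any treatment before MRI in this cohort. The documents do not support that inference.

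**Conclusion.** The point holds as a criterion fixed too narrowly. Read literally, the eligibility rules can admit tumours imaged after chemotherapy alone or radiotherapy alone, and no other rule prevents it. Those images could weaken or distort the T2WI–MSI relation in both cohorts.

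The consequence is possible, not demonstrated. A reader might conclude that the model is in fact trained and tested on treated tumours. The documents do not show that any such patient was enrolled, or how many. The fall from AUC 0.85 to about 0.83–0.79 rests on an assumed 5–20% share, equal in both groups, with no signal in treated tumours. If the share is zero, the effect is zero and one clarifying line settles the matter.

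**What to change.** Reword exclusion (2), as a rule for selecting images, so that it covers any anti-tumour treatment for the rectal cancer before the study MRI. Apply it from the treatment records before the 70/30 split, and report the number removed, by MSI status, in the flowchart. If the present term was meant in the wide sense, say so and give the count.

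Sections 2.4.1 and 2.6.2 must also be reconciled on whether the MRI window runs back from surgery only or from surgery or biopsy, since this bears on whether a scan could follow treatment.

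The cost is one line of eligibility text, a record check, and the loss of any such patients. If 5% to 20% of the planned 330 were removed and not replaced, power would fall from about 86% to between 84% and 76% on the two-sided calculation above. The study is retrospective with no intervention, so patient care is not affected.

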### Intervention

2.5

This study is a retrospective analysis of MRI T2WI images, with no intervention measures for patients.

### Radiomics analysis (Fig. 2)

2.6

#### Clinical and pathological data

2.6.1

Clinical data include: age, sex, carcinoembryonic antigen, and carbohydrate antigen 19-9.

**Figure 2 F2:**
[figure not shown]
The radiomics analysis framework in this study.

Pathological data include: tumor differentiation degree, T stage, Ki-67 expression, and MSI status. Considering the Bethesda guidelines for CRCs suggesting that the terms MSI-H or MSI-low (MSI-L) be discontinued and MSI-L tumors be included with MSS tumors, the MSI-H was regarded as MSI and MSI-L was regarded as MSS in this study.

#### MRI image acquisition and segmentation

2.6.2

All patients underwent MRI scan following protocol for RC within 2 weeks before surgery or biopsy. By using the ITK-SNAP software (v3.6.0, http://www.itksnap.org), the tumor region was manually segmented volumetrically by a radiologist with more than 10 years of experience in abdominal imaging on all oblique axial (angulated perpendicular to the long axis of the rectal tumor) of T2WI slices. The necrosis area, intraluminal air regions, and uninvaded rectal wall were excluded from the ROIs with caution. In case that the boundary was uncertain, a final decision was made by another radiologist with 20 years of experience in abdominal diagnosis.

#### Feature extraction

2.6.3

To achieve a standard normal distribution of image intensities, MRI scans for each patient were normalized with *z*-scores. Feature extraction was performed using an open-source Python package (PyRadiomics version 2.1.2, https://github.com/Radiomics/pyradiomics), radiomics features including shape, first-order intensity statistics, and texture features were automatically extracted from the manually segmented tumor regions.

#### Inter- and intraobserver reproducibility evaluation

2.6.4

To evaluate the reproducibility and accuracy of image segmentation and feature extraction, we randomly selected 50 MR scans and performed double-blind manual segmentation by 2 radiologists repeatly. The radiomics features from the 50 paired segmentation results were automatically extracted, and intraclass correlation coefficients (ICC) was used to access the inter- and intraobserver agreement.

#### Feature selection

2.6.5

The feature extraction and selection process were performed using Python 3.6.0 (www.python.org). Only the extracted radiomics features with good reproducibility (ICC >0.75) were selected for further analysis. To prevent overfitting of the model, the variance threshold approach (scikit-learn 0.22.1, sklearn. feature_selection module) was used to remove all features whose variance did not meet a certain threshold based on the training queue. The least absolute shrinkage and selection operator algorithm was used to select the key radiomics features that were the most closely associated with determination of MSI status in RC.

#### Development of the radiomics models

2.6.6

We used multivariable logistic regression analysis to develop 3 models: radiomics clinicopathological model, radiomics imaging model, and combined model integrating radiomics imaging and clinical information. Selected radiomics feature values were standardized to the (0, 1) interval to avoid redundancies and inconsistencies. The radiomics clinicopathological model was developed with clinical parameters. The radiomics model was constructed with selected features. The combined model was built with both selected radiomics features and clinical parameters. The 5-fold cross validation approach was used in the training/validation cohort to better train our model and build it more robustly. The development and validation of the radiomics models were performed with the InferScholar platform version 3.1 (InferVision, China).

### Outcome measure

2.7

The radiomics model which identify potential differences between RC without MSI-H group and RC with MSI-H group will be the outcome measure.

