### Statistical analysis

2.10

The ROC curve analysis was conducted, and AUC, accuracy, sensitivity, and specificity were calculated to evaluate the diagnostic performance of each model. Mann–Whitney *U* test and Chi-squared test or Fisher exact test were performed to evaluate the differences in variables with a continuous distribution across categories and the association among categorical variables, respectively. A 2-sided *P*-value of <.05 was considered as statistically significant. Prism 5 for Windows (Version 5.01) and MedCalc (Version 18.11.3) were used for statistical analysis.

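### The AUC benchmark of 0.70 that fixed the sample size is not carried into the outcome or the analysis, so the stated 95% power describes a test the plan never specifies

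*Protocol article*

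**What the plan says.** - **Hypothesis** (Introduction): "a simple radiomics model based on only T2WI images can accurately evaluate the MSI status of RC preoperatively". No section gives an AUC that would count as accurate.
- **Sample size** (2.9): the procedure is "Test for 1 receiver operating characteristic (ROC) curve analysis". It is meant to "detect a difference of the null hypothesis (area under the curve [AUC] = 0.70) and the alternative hypothesis (AUC = 0.85"), and "a sample of 33 from the MSI group and 297 from the MSS group could achieve 95% power".
- **Outcome** (2.7): "The radiomics model which identify potential differences between RC without MSI-H group and RC with MSI-H group will be the outcome measure". This names a model, not a measured quantity, and gives no threshold.
- **Analysis** (2.10): "AUC, accuracy, sensitivity, and specificity were calculated to evaluate the diagnostic performance of each model". Mann–Whitney, chi-squared and Fisher tests on variables follow, then a general two-sided 0.05 significance level. No null value, confidence-limit criterion or success rule is given for the AUC.
- **Where performance is judged** (Abstract, Method): the testing cohort, 30% of patients, on AUC, sensitivity, specificity and accuracy.

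As an AUC benchmark, 0.70 appears only in section 2.9.

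**The concern.** By choosing 0.70 as the null, section 2.9 treats an AUC of 0.70 as not good enough. A reader would expect the outcome and analysis sections to ask whether the model beats 0.70. Neither does. The claim of accuracy can then rest on a point estimate, or on any demonstration that the model separates the two groups, which is a much lower bar than the one that justified 330 patients. The 95% power would be quoted for a test nobody has committed to run, and no stated rule would limit how often a model at the protocol's own null is declared a success.

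**Working it through.** **Inputs.** From 2.9: null AUC A0 = 0.70, alternative A1 = 0.85, m = 33 MSI, n = 297 MSS, power 95%. From 2.10: two-sided 0.05, assumed to apply to the sizing as well. From the Abstract: a 30% testing cohort. Carrying over the 1:9 ratio (assumption) gives 0.3 × 33 = 9.9 and 0.3 × 297 = 89.1, so about 10/89.

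**Formula.** Power = Φ[(A1 − A0 − 1.96·SE0)/SE1], with SE0 and SE1 the standard errors of the AUC at A0 and A1. Three variances were used: Obuchowski–McClish binormal (equal variances), Hanley–McNeil, and the Obuchowski exponential approximation.

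**1. The plan's own figure (33/297, 0.70 vs 0.85).**
- Binormal: SE0 = 0.0466, SE1 = 0.0341. (0.15 − 1.96 × 0.0466)/0.0341 = 1.72, so power is 95.7%. The stated 95% is reproduced.
- Hanley–McNeil gives 86.1% and the exponential approximation 86.0%.

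The sizing figure is sound under the binormal variance, for a test against 0.70.

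**2. A model at the protocol's null (true AUC 0.70), if success means beating 0.50.** The document writes no such test; this is one reading of 2.7. The formula is the same, with A0 = 0.50 and A1 = 0.70.

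| Variance | 33/297 | 10/89 |
|---|---|---|
| Binormal | (0.20 − 1.96 × 0.0518)/0.0466 = 2.11 → 98.3% | (0.20 − 1.96 × 0.0941)/0.0848 = 0.18 → 57.3% |
| Exponential approximation | 97.2% | 56.8% |
| Hanley–McNeil | (0.20 − 1.96 × 0.0531)/0.0528 = 1.82 → 96.5% | (0.20 − 1.96 × 0.0968)/0.0963 = 0.11 → 54.3% |

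A simulation (binormal scores, DeLong standard error, Wald limit, 20,000 replicates) gives 97.6% and 60.8%. Even a true AUC of 0.65 would pass in about 80–84% at 33/297 and 34–36% at 10/89 by the formulas.

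**3. The same model, if success means exceeding 0.70.** The nominal rate is 2.5%. The simulated DeLong Wald lower limit exceeds 0.70 in about 4% of studies at 33/297 and about 7% at 10/89, so the plain DeLong limit is anti-conservative in the small cohort. At 10/89 a logit-transformed DeLong limit gives 3.9%, and tests using the null variance give 0.8% (Hanley–McNeil) to 1.9% (binormal).

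**4. Observed AUC needed.**
- 33/297: about 0.60 to beat 0.50. To beat 0.70: 0.70 + 1.96 × 0.0466 = 0.79 (binormal) to 0.70 + 1.96 × 0.0528 = 0.80 (Hanley–McNeil).
- 10/89: 0.68–0.69 to beat 0.50. To beat 0.70: about 0.83 with a DeLong Wald limit, 0.70 + 1.96 × 0.0848 = 0.87 (binormal) or 0.70 + 1.96 × 0.0963 = 0.89 (Hanley–McNeil).

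**5. Power against 0.70 in the testing cohort (10/89, true AUC 0.85).**
- Binormal: (0.15 − 1.96 × 0.0848)/0.0619 = −0.26 → 39.7%.
- Exponential approximation: 34.0%.
- Hanley–McNeil: (0.15 − 1.96 × 0.0963)/0.0781 = −0.50 → 31.0%.
- Simulated: about 64% with the DeLong Wald limit, at the inflated error rate in step 3; 47% with the logit-transformed limit.

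**The case against.** The best defence is that this is an omission in a condensed article. Section 2.9 names a one-sample ROC test and its null, so the intended hypothesis can be inferred. Section 2.10 does report the AUC, so anyone can set it beside 0.70. The choice of interval and of paired model comparisons is ordinary analysis-plan detail.

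Much of this stands, and it rules out three stronger readings.

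- A reader might infer that the plan states two competing nulls, 0.70 and 0.50. It does not. The only AUC null written anywhere is 0.70; section 2.7 gives no null, test or value.
- A reader might take the 97% and 54–61% as the plan's false-success rate under its own 0.05 rule. That rule follows the Mann–Whitney, chi-squared and Fisher tests and is not tied to the AUC, so these figures illustrate one reading of 2.7.
- A reader might add that the plan leaves open which of its three models carries the hypothesis. The Introduction and the aim (2.1) specify a T2WI-based model, and 2.6.6 uses the term radiomics model for the one built from selected image features, apart from the clinicopathological and combined models.

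What the defence does not answer is that the article does publish an outcome definition and an analysis section, and neither contains the benchmark that fixed the sample size. A reader who compares the AUC with 0.70 informally is not applying a prespecified criterion.

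**Conclusion.** The point holds as a failure to carry the 0.70 benchmark from 2.9 into 2.7 and 2.10. That conclusion rests on the text alone. The 95% power is reproducible (95.7%, binormal, two-sided 0.05), but for a test the plan does not set. The size of the consequence depends on two assumptions: that separating the groups means AUC against 0.50, and that the 1:9 ratio carries into the testing cohort. Under these, a model with true AUC 0.70 would pass in about 97% of studies at 33/297 and about 54–61% at 10/89, whereas a valid test against 0.70 would pass it in 2.5%. This should be corrected, since it decides what the study can conclude.

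**What to change.** - **2.7:** *Primary outcome: AUC of the T2WI radiomics imaging model in the testing cohort.*
- **2.10:** *The hypothesis is supported only if this AUC is significantly above 0.70 at two-sided 0.05. The clinicopathological and combined models are secondary.* Name a test or interval that holds its error rate with about 10 MSI cases. A score-type (null-variance) method does so in the check above. A logit-transformed interval comes closer to nominal than a plain DeLong Wald limit but was still somewhat liberal (3.9% against 2.5%), so its error rate should be checked before it is adopted.
- **2.9:** State that the 95% power applies to 33/297, and give the power for the testing cohort.

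**Cost.** A few sentences and no new data. The bar becomes stricter: at 10/89 an observed AUC of about 0.83–0.89 is needed, depending on the variance method. The change also exposes low power in the cohort where the test is run: about 31–40% with null-variance tests, or about 64% with a DeLong Wald limit that is anti-conservative. With the test placed there, a true AUC of 0.85 could well fail to be confirmed, and the report should say so.
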